### Data monitoring

The trial is organized by a team comprised of a principal investigator, a general investigator, and other participants who take part in the design and implementation of the study. For quality control purposes, an external independent physician not involved in the trial will be responsible for data monitoring. Monitoring includes assessment of the progress of the study and verification of accuracy as well as the completeness of recorded data. After completion of the study, we will submit the original data and results to the scientific management committee, and after the publication of results, we will disclose original data and results to the public.

### Statistical analysis

After completing the trial, the research team will collaborate with medical statisticians to analyze the data. Statistical analysis will be performed on the basis of intention to treat. SPSS 20.0 software will be used for analysis. The majority of data will be collected and recorded onto the CRF. Before analyzing the data, the pattern of missing data will be evaluated. Analyzation of graphics and data acquired from the EIT machine will be executed by a computer expert familiar with machine principles. Kolmogorov-Smirnov analysis will be used to detect the distribution of all the data. Normally distributed data will be expressed by the mean and standard deviation (SD), while skewed data will be expressed by their median and interquartile range. Unpaired *t* test will be used for univariate analysis of normally distributed data. Pearson correlation test will be employed to test the correlation between two variables. Mann-Whitney *U* test and Wilcoxon signed-rank test will be applied for skewed data. Categorical variables will be assessed by Fisher’s exact test, chi-square tests, or relative risk, if appropriate. 95% CI will be employed to express statistical uncertainty. *P* value <0.05 shall be regarded as significant.

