### Study endpoints

The primary endpoint of the study is the amount of calculated atelectasis, corresponding to the percentage of collapsed lung mass, which is obtained through the following steps. The baseline lung volume and its associated parameters of all patients are measured before and after anesthesia induction by Drager’s EIT. Immediately after extubation and 2 h postoperation, the proportion taken up by collapsed lung mass is measured by EIT. The amount of atelectasis is calculated via dividing the area occupied by non-ventilated lung mass by baseline lung volume.

Secondary endpoints consist of the value of individualized PEEP, oxygenation index (PaO_2_/FiO_2_), respiratory parameters, blood gas analysis indicators, anesthesia-associated parameters, and hygienic index.

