### Study visits and data collection

We visit patients preoperatively, intraoperatively, and postoperatively on postoperative days 1 and 3 and at discharge (Table 1). At all the above-listed points in time, patients’ data are collected and recorded.
Preoperative indicators: gender, age, weight, height, body mass index, smoking status, assessment of difficult airways, ASA grade, heart rate, blood pressure, body temperature, blood routine, blood biochemistry, coagulation function, and other past histories.Intraoperative indicators: heart rate, blood pressure, pulse oxygen saturation, bispectral index, respiratory parameters, PEEP settings, all data measured by EIT, transfusion of blood products, volume of fluids and dosage of drugs administered throughout the duration of anesthesia (e.g., crystalloid fluid, colloid fluid, analgesic drugs, sedative drugs, muscle relaxants, vasoactive drugs), urine output, duration of operation (from incision to closure), etc.Postoperative indicators: duration of ICU treatment, length of hospital stay, hospitalization expenses, presence of complications, and adverse events.

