### Sample size calculations

The primary endpoint of this study is the ratio of collapsed lung mass to normal lung tissue, which is measured and automatically calculated via using EIT before anesthesia and immediately after endotracheal extubation. According to our pre-experimental results of this study, the lung collapse area in the Cstat-PEEP group was 6.5%, while that in the EIT-PEEP group was 6.2%. We apply a noninferiority test. We hypothesize that compared with the ratio of lung collapse area in the EIT-PEEP group, the ratio of lung collapse area in the Cstat-PEEP group will increase by no more than 2% (i.e., the ratio of lung collapse area in Cstat-PEEP group within 8.2% is non-inferior). We choose a two-sided significance level of 0.025 (*α*) and *β*= 0.2, with a power of 80%. Using the PASS 11.0 software, a sample size of 64 is calculated for each group. Taking a 10% dropout rate in patients’ follow-up into account, a final sample size of 70 is required for each group.

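### Only unadjusted two-group tests are named for continuous outcomes, although pre-titration EIT values and BMI are already planned; a prespecified ANCOVA could gain precision against the 2-point margin at little cost

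*Protocol article*

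**What the plan says.** The Statistical analysis section lists tests by type of data, after a Kolmogorov-Smirnov check. For continuous data it states: "Unpaired *t* test will be used for univariate analysis of normally distributed data" and "Mann-Whitney *U* test and Wilcoxon signed-rank test will be applied for skewed data". It names no covariate-adjusted model, and it does not say which test is the primary analysis.

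Two sections describe EIT data obtained before titration. Study endpoints says: "The baseline lung volume and its associated parameters of all patients are measured before and after anesthesia induction". Sample size calculations describes the primary ratio as "measured and automatically calculated via using EIT before anesthesia and immediately after endotracheal extubation". Study visits and data collection lists the preoperative variables, among them "gender, age, weight, height, body mass index, smoking status".

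Baseline information does enter the endpoint once, as a denominator. Atelectasis is obtained by "dividing the area occupied by non-ventilated lung mass by baseline lung volume".

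The decision rule is non-inferiority. In the pre-experiment "the lung collapse area in the Cstat-PEEP group was 6.5%, while that in the EIT-PEEP group was 6.2" (per cent), and the hypothesis is that "the ratio of lung collapse area in the Cstat-PEEP group will increase by no more than 2" (percentage points, since the limit is put at 8.2% against 6.2%).

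**The concern.** Non-inferiority is claimed if the upper confidence limit for the difference in collapse lies below 2 points, so the width of the interval matters as much as the point estimate. If a value taken before the arms diverge predicts collapse after extubation, an unadjusted comparison leaves that explained variation in the error term and the interval is wider than it need be.

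Dividing by baseline lung volume does not serve this purpose. It scales the outcome to lung size; it does not account for how much lung was already collapsed. Randomisation is in blocks of four, with no stratification described, so the design does not balance BMI or baseline collapse either.

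At stake is power. The design has 80% at 64 per arm, and 70 per arm less 10% leaves 63. A second, smaller point is that a Mann-Whitney p value gives no mean difference to compare with 2 points, whereas an ANCOVA does.

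**Working it through.** **Inputs from the article (Sample size calculations).** Margin 2 points; expected difference 6.5 − 6.2 = 0.3 points; power 80%; 64 per arm before dropout. Alpha is given as 0.025 and called two-sided. One-sided 0.025, which matches the planned 95% CI, is used first, and the literal reading (one-sided 0.0125) is checked below.

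**Not in the article.** The SD and the correlation r. The SD is solved back from the stated sample size. For r, a range of 0 to 0.7 is assumed.

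**Step 1, the plan's own figure.** Without an SD, 64 cannot be reproduced forward. Solving back:

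SD = (2 − 0.3) × √(64/2) / (1.960 + 0.842) = 1.7 × 5.657 / 2.802 = 3.43 points.

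**Step 2, unadjusted precision.** 95% CI half-width = 1.960 × 3.43 × √(2/64) = 1.189 points. Non-inferiority is then shown if the observed difference is below 2 − 1.189 = 0.811.

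**Step 3, with baseline adjustment.** Residual SD = SD × √(1 − r²), so the half-width scales by √(1 − r²). Power = Φ(2.802/√(1 − r²) − 1.960).

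| r (assumed) | √(1 − r²) | Half-width | Largest observed difference that passes | Power at 64 per arm | n per arm for 80% |
|---|---|---|---|---|---|
| 0 | 1.000 | 1.189 | 0.811 | 80.0% | 64 |
| 0.1 | 0.995 | 1.183 | 0.817 | 80.4% | 64 |
| 0.2 | 0.980 | 1.165 | 0.835 | 81.6% | 62 |
| 0.3 | 0.954 | 1.135 | 0.865 | 83.6% | 59 |
| 0.5 | 0.866 | 1.030 | 0.970 | 89.9% | 48 |
| 0.7 | 0.714 | 0.849 | 1.151 | 97.5% | 33 |

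**Step 4, sensitivity to the alpha and true-difference readings.** One-sided 0.0125 with a true difference of 0.3 implies SD 3.12 and gives power of 81.7%, 83.9%, 90.6% and 98.1% at r = 0.2, 0.3, 0.5 and 0.7. A true difference of 0 implies SD 4.04 (one-sided 0.025) or 3.67 (one-sided 0.0125), and power is the same as above for the respective alpha. The width ratios do not change in any variant.

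**Step 5, cost if the covariates predict nothing.** With 128 patients, one uninformative covariate widens the interval by about √(1 + 1/124) = 1.004, or 0.4%. If BMI is a second uninformative covariate, the factor is about √(1 + 2/123) = 1.008, or 0.8%.

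**Step 6, which EIT value.** The Discussion cites non-ventilated lung rising from 1% to 11% in obese patients under anaesthesia and ventilation. An awake value near 1% may lie close to its floor, vary little and correlate weakly with the outcome. The post-induction value has more room to vary. In both arms titration begins only once pneumoperitoneum is established, so a value taken at induction precedes the point where treatment differs.

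**The case against.** The strongest reply is that nothing here is wrong. An unadjusted comparison is valid under 1:1 randomisation. The Statistical analysis section is a general menu for all variables, and an analysis plan that is not shown may name an adjusted model. All of this stands, and it makes the point one of efficiency. What remains is that the article does commit to named tests for continuous data, and all of them are unadjusted.

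A reader might infer three stronger things.

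- **That adjustment is sure to narrow the interval.** The article gives no correlation. At r of 0.2 or less the narrowing is at most 2%. The floor suggested by the Discussion, with recruitment manoeuvres, titrated PEEP and surgery in between, makes a low value plausible.
- **That chance imbalance in BMI or baseline collapse biases the result.** It does not. Imbalance affects the difference only in proportion to how prognostic the variable is, and the unadjusted interval and error rate already allow for it.
- **That baseline collapse is certainly recorded as a percentage in everyone.** Study endpoints mentions baseline lung volume and associated parameters, and times collapsed lung mass at extubation and 2 h. The wording in Sample size calculations supports a pre-anaesthesia ratio, but could also describe the two inputs to a single ratio. EIT measurement before titration in all patients is clear; which parameter serves as covariate must be stated.

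**Conclusion.** The point holds as an efficiency improvement: the named analysis leaves planned, pre-titration information unused in a comparison that depends on interval width. The possible gain at 64 per arm runs from nothing (r near 0) through about 4 percentage points of power (r = 0.3) to about 10 (r = 0.5) and 18 (r = 0.7). The interval narrows by 13% or more only if r is at least 0.5. These figures rest on the back-solved SD of 3.43 and on assumed correlations, while the proportional change in width depends on r alone. The loss if the covariates prove useless is under 1% of interval width. The documents do not support calling the unadjusted t test invalid or biased.

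**What to change.** Before any outcome data are examined, prespecify the primary analysis as an ANCOVA of post-extubation collapse (%) on arm, with two continuous covariates:

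- one EIT baseline value taken before titration, either pre-induction or post-induction, chosen and defined in advance (the post-induction value may be less affected by a floor);
- BMI.

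Report the adjusted difference and its confidence interval against +2 points, and give the unadjusted difference as a sensitivity analysis.

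No new data collection is needed if the chosen EIT value is among those already recorded. The cost is a documented amendment to the analysis wording (the article says the trial is ongoing), a simple rule for missing baseline values, and the small loss of precision in Step 5 if the covariates prove uninformative. Because skewed data are anticipated, the amendment should also say how the linear model will be checked.

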## Discussion

This trial is sufficiently powered to test the hypothesis that an individualized PEEP titrated by maximizing Cstat is not inferior to individualized PEEP determined by EIT in terms of lowering the proportion of collapsed lung tissue, for obese patients. The result will prove that the method of best Cstat titration iPEEP is simple and effective in clinical practice.

According to a population-based study, in 2014, approximately 10.8% of men and 14.9% of women are obese globally [13]. In obese patients, the respiratory compliance is further limited by the cephalic movement of the diaphragm. In addition, the FRC and alveolar ventilation volume of obese patients are much lower than their non-obese counterparts. The incidence of atelectasis in obese patients under general anesthesia is as high as 90% [14]. In obese patients under general anesthesia and mechanical ventilation, the proportion of normal ventilated lung tissue drops from 71 to 50%, while the proportion of insufficiently ventilated lung mass increases from 28 to 39%, and the proportion of non-ventilated lung tissue elevates from 1 to 11%. In sharp contrast, the proportion of atelectatic lung mass is only 3% in normal weight patients under general anesthesia and mechanical ventilation [15].

Because airway pressure required to keep lung units from collapsing is much lower than the pressure needed to recruit atelectatic lung units, recruitment maneuver could significantly improve ventilation. Applying PEEP after a successful recruitment maneuver could prevent the rapid reformation of atelectasis, especially when the fraction of inspired oxygen is as high as 100% [16]. Applying PEEP alone alleviates the reduction of end-expiratory lung volume and lung elastance imposed by pneumoperitoneum on obese patients, but fails to reduce an atelectatic fraction of the lung tissue [17]. Compared to PEEP applied alone, the combination of PEEP and recruitment maneuver leads to greater enhancement in lung elastance and results in lower airway pressure as well as resistance in obese patients undergoing laparoscopic surgery.

However, no agreement has been reached concerning the optimal PEEP for obese patients. High PEEP is associated with improved intraoperative oxygenation and lung elastance as well as a reduced proportion of atelectatic lung units, especially for obese patients [18]. But too high PEEP may lead to overextension of lung units, which aggravate lung injury. From the PROBESE study, compared to a lower PEEP, a fixed higher PEEP did not decrease the incidence of PPCs in obese patients [1].

According to the literature, it is highly unlikely to find a fixed PEEP which suits all patients with significant variation in PEEP requirement caused by individual characteristics, such as abdominal content, chest wall shape and dimensions, pleural pressures, and lung weights [19]. Thus, an individualized ideal PEEP may be superior to a fixed PEEP level. Relevant studies have discovered that compared with applying a fixed PEEP, applying individualized PEEP improves oxygenation and respiratory compliance, reduces the fraction of dead space, minimizes atelectasis, optimizes ventilation distribution, and ameliorates lung injury by lowering driving pressure [20, 21].

No consensus has been reached concerning the ideal way to select the ideal and individualized PEEP. And, many ways effective for selecting individualized PEEP for normal weight patients may not be appropriate for obese patients. For instance, determining individualized PEEP as the pressure nearest to the low inflection point of the pressure-volume curve underestimates the PEEP required by obese patients [22]. Electrical impedance tomography (EIT) is deemed superior to traditional ways of individualized PEEP titration by many studies [23, 24]. EIT is a clinical imaging tool that monitors local ventilation distribution. It enables the continuous measurement of local lung ventilation changes resulting from the application of recruitment maneuvers and PEEP as well as adjustments in tidal volume and fraction of inspired oxygen. Traditional ways of PEEP titration may provide misleading information by averaging contradicting pathological characteristics of different lung units, such as overdistention and atelectasis. In contrast, EIT monitors regional lung ventilation and can detect pulmonary heterogeneity in a dynamic process. It has gained widespread interest in guiding lung-protective ventilation in obese patients. However, the EIT instrument is unaffordable by many clinical institutions, which limits its use in routine clinical practice. At the same time, the bandage of the EIT machine conflicts with the field disinfection of many operations in the chest or abdomen, which also limits its application in the perioperative period. So alternative ways to titrate PEEP both affordable and effective need to be found out. This study is going to test the efficacy of determining individualized PEEP during an incremental titration procedure guided by optimal static lung compliance by comparing it with the PEEP titration strategy directed by EIT.

In our previous study [25], it has been found that when applying optimal static lung compliance titration iPEEP in obese patients undergoing laparoscopic surgery, the PEEP value was about 10.5 cmH_2_O. Compared with PEEP 5 cmH_2_O, it could significantly improve the oxygen index and respiratory function of obese patients during and after laparoscopic surgery, combined with other lung protective strategies. These data provide evidential support for us to use the best static lung compliance method to titrate iPEEP.

In conclusion, this study aims to verify the following hypothesis: individualized iPEEP titrated to optimal static lung compliance is not inferior to individualized iPEEP obtained during a titration procedure guided by EIT, in terms of improving intraoperative oxygenation and ameliorating postoperative atelectasis in obese patients undergoing laparoscopic surgery. This study will provide a convenient and feasible strategy for individualized PEEP titration in obese patients. The result shall provide direct evidence to further refine lung-protective ventilation strategies in obese patients and exploit the significance of lung-protective ventilation in ERAS in obese patients.

### Trial status

We enrolled the first participant of the trial on November 15, 2020, the protocol version is the first version, and the version number is V1.0/2020.06.26. We will complete the recruitment on September 17, 2022. This trial is still ongoing.

## Data Availability

Data will be disclosed to the public after the complication of the trial. After the study is completed and the results are published, the data will be obtained by contacting the corresponding author.

## Abbreviations

PPCs: Postoperative pulmonary complications
iPEEP: Individualized positive end-expiratory pressure
Cstat: Static lung compliance
FiO2: Inspiratory fraction of inspired oxygen
EIT: Electrical impedance tomography
PBW: Predicted body weight
RM: Recruitment maneuvers
VT: Tidal volume
CRF: Case report forms
ARISCAT: The assess respiratory risk in surgical patients in catalonia
BMI: Body mass index
COPD: Chronic obstructive pulmonary disease
Cstat-iPEEP: Optimal static lung compliance-directed iPEEP titration group
EIT-iPEEP: Electrical impedance tomography-guided iPEEP titration group
VAS: Visual analog scale
PSC-VC: Pressure-control-volume compensation mode
Pplat: Plateau airway pressure
Ppeak: Peak airway pressure
1:E: Ratio between inspiratory and expiratory time
PaO_2_: Partial pressure of arterial oxygen
PCT: Procalcitonin
